**Methods:**

A multi-centre, individually randomised, open-label trial will be conducted in seven sites in six countries: Bangladesh, Ethiopia, India (two sites), Nigeria, Pakistan and Tanzania. A common protocol will be used with the same study design, including the participants, intervention, comparison, outcomes, quality control, and analysis procedures. 0-59 days old infants presenting with moderate-mortality risk signs (low body temperature (<35.5°C), movement only when stimulated, stopped feeding well) or two or more signs of clinical severe infection (CSI) will be assessed and pre-enrolled. After 48 hours of hospital stay, clinically stable infants with a negative C-reactive protein test will be randomised either to hospital discharge on oral amoxicillin (intervention) or continued hospitalisation (control) arm. The intervention arm will receive oral amoxicillin for five days, whereas the control arm will receive injection gentamicin plus injection ampicillin for five more days plus supportive therapy if needed. We plan to enrol 5250 eligible young infants, 2625 infants in each of the two study arms. An experienced, well-trained independent outcome assessor will visit all enrolled cases on days 4, 8 and 15 after the initiation of treatment to assess the study outcomes in both intervention and control arms. The primary outcome of poor clinical outcome defined as death between randomisation and day 15 of initiation of treatment, deterioration during the 7-day treatment period, or persistence of the presenting sign of CSI at the end of the 7-day treatment period will be compared to assess if an early discharge and outpatient treatment leads to superior or at least non-inferior clinical outcome than continued inpatient treatment. The harmonisation of activities, including methods and processes, will be carried out diligently. Central training will be conducted by the WHO coordinating team, a central data coordination centre to collate all data, standardisation exercises for all clinical signs and internal and external monitoring. All the selected sites have extensive research experience. Through regular online and physical meetings, data-based monitoring, and physical site visits by WHO monitors, quality assurance and harmonisation will be ensured. This trial has been approved by the WHO and local site institutional ethics committees.

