## METHODS

### Research question

Among hospital-admitted young infants 0-59 days old with any moderate-mortality risk sign or two or more low-mortality risk signs who clinically improve 48 hours after initiation of treatment and have a negative C-reactive protein (CRP) (population), are discharged from the hospital on oral amoxicillin at home for the next five days (intervention), compared with continued hospital management for next five days (control), non-inferior in terms of poor clinical outcome (outcome)?

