### Randomisation to treatment arms

WHO staff in Geneva not associated with site work prepared the randomisation list in blocks of four, six and eight and shared it with the Regional Triangle Institute (RTI), the study Data Coordination Centre (DCC). Allocation concealment was ensured using QR randomisation codes. Randomization was in a 1:1 ratio. RTI produced a list of encrypted QR codes and has these printed on labels based on the randomisation scheme for each study site. RTI transmitted the printed QR code blue colour labels to the sites.

Each hospital within a study site will have a single set of QR codes that all screening and enrolment team members must use, even if the screening and enrolment are taking place in different locations within the hospital. After determining eligibility, the data collector will take the QR code label next in the sequence from the list at their facility and scan this to obtain the randomisation number.

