### Sample size

We will enrol a total of 5250 participants in the trial across study sites. Power calculations assumed 1:1 randomised, a one-sided type I error rate α of 0.025 (equivalent to a two-sided 95% confidence interval), and a loss to follow-up or withdrawal rate of 10%. The non-inferiority margin for the poor clinical outcome was selected as a relative risk of 1.40 for the outpatient group as compared to the standard inpatient group. This margin was selected based on the previous trials [6,7]. **Table 3** presents statistical power for trial outcomes varying the potential cumulative incidence of poor clinical outcomes in the standard inpatient group. We will have >88% power to test for non-inferiority if the cumulative incidence of poor clinical outcomes is 5-10% in the inpatient group.

**Table 3 T3:** Statistical power calculations for incidence of poor clinical outcome

		Cumulative incidence of poor clinical outcome in standard inpatient arm		
		**10.0%**	**7.5%**	**5.0%**
Statistical power for poor clinical outcome	Noninferiority margin: Relative risk of 1.40	96.6%	97.5%	88.4%

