### Data analysis

Simple comparisons of means and proportions by intervention and control treatment arms will be carried out to evaluate the baseline comparability of the two groups. The Kolmogorov-Smirnov test of normality will be used to test the normality of the data. The primary analyses will be per-protocol to compare treatment outcomes by comparing proportions of poor clinical outcomes (including deaths and deterioration) between intervention and control arms using the Chi-square test, setting statistically significant as *P* <0.05. An intention-to-treat analysis will also be conducted. The clinical outcomes between control and intervention treatment arms will be compared, and the difference in the risk of poor clinical outcomes together with 95% confidence intervals, will be calculated. Secondary analyses will be performed to identify predictors of poor clinical outcomes.

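### The named primary test (chi-square for equality) and effect scale (risk difference without a margin) do not match the non-inferiority design with its relative-risk margin of 1.40

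*Protocol article*

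**What the plan says.** Three places in the protocol article set up a non-inferiority trial.

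- The Research question asks whether early discharge is "non-inferior in terms of poor clinical outcome (outcome").
- The Methods paragraph of the abstract widens this slightly, to whether early discharge "leads to superior or at least non-inferior clinical outcome than continued inpatient treatment".
- The Sample size section fixes the threshold, "The non-inferiority margin for the poor clinical outcome was selected as a relative risk of 1.40", and the error rate, "a one-sided type I error rate α of 0.025 (equivalent to a two-sided 95% confidence interval").

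The Data analysis section then describes the primary analysis. It is per-protocol, with intention-to-treat alongside, and compares proportions "between intervention and control arms using the Chi-square test, setting statistically significant as" P <0.05. For estimation, "the difference in the risk of poor clinical outcomes together with 95% confidence intervals, will be calculated". That section does not mention non-inferiority, a relative risk, the value 1.40, or any comparison of a confidence limit with a margin. No other section shown supplies one.

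**The concern.** A chi-square test at P <0.05 has equal risks as its null hypothesis. A non-inferiority test has as its null hypothesis that home treatment raises the risk by the margin or more. The two can disagree in both directions. A non-significant chi-square may accompany an interval that reaches well beyond 1.40, and a significantly worse result may still lie inside the margin.

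The promised interval does not close the gap, because it is on a different scale from the margin. A relative risk of 1.40 has no single equivalent in percentage points. It is 0.40 times the control risk: 2.0 points at 5%, 3.0 at 7.5% and 4.0 at 10%.

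The primary outcome includes infant death, and the result is meant to inform a review of WHO guidance. The rule by which early discharge is declared acceptable should therefore be the rule the trial was sized for, and it should be named as such.

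**Working it through.** **Inputs.** "We will enrol a total of 5250 participants in the trial across study sites"; "Randomization was in a 1:1 ratio", so 2625 per arm; 10% loss, so 2625 × 0.9 = 2362.5 analysed per arm; margin 1.40; one-sided 0.025 (z = 1.96); control risk *p* of 5%, 7.5% or 10% (Sample size and Table 3).

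**Step 1: reproduce the stated power.** On the risk-difference scale, with margin 0.40*p* and no true difference:

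power = Φ(0.40*p* / √(2*p*(1−*p*)/n) − 1.96), n = 2362.5

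- 5%: Φ(0.0200/0.00634 − 1.96) = Φ(1.19) = 88.4% (stated 88.4%)
- 7.5%: Φ(0.0300/0.00766 − 1.96) = Φ(1.95) = 97.5% (stated 97.5%)
- 10%: Φ(0.0400/0.00873 − 1.96) = Φ(2.62) = 99.6% (stated 96.6%)

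Two of the three entries reproduce, so the trial was sized for a margin test and not for a test of equality. The 10% entry does not reproduce on this scale and is lower than the 7.5% entry.

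**Step 2: power when the margin is tested as a relative risk.** On the log scale:

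power = Φ(ln 1.40 / √(2(1−*p*)/(n*p*)) − 1.96), ln 1.40 = 0.3365

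- 5%: Φ(0.3365/0.1268 − 1.96) = 75.6%
- 7.5%: Φ(0.3365/0.1022 − 1.96) = 90.9%
- 10%: Φ(0.3365/0.0873 − 1.96) = 97.1%

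Step 1 treats 0.40*p* as a known number of points. Step 2 does not, and this is why its power is lower.

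**Step 3: compare the two decision rules.** Rule A is the two-sided chi-square at 0.05. Rule B is an upper 95% limit for the relative risk (log scale) below 1.40. I summed binomial probabilities over all pairs of event counts, with 2362 per arm.

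| Control risk | True RR 1.40: A non-significant | True RR 1.40: B met | True RR 1.0: A non-significant and B not met |
|---|---|---|---|
| 5% | 17% | 2.5% | 22% |
| 7.5% | 4.9% | 2.5% | 6.9% |
| 10% | 1.1% | 2.5% | 0.6% |

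Disagreement the other way: at 10% control risk and a true relative risk of 1.2, about 5% of trials are significantly worse by chi-square yet meet the margin.

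**Step 4: two possible results, 2362 per arm.**

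- 142 events at home against 118 in hospital: P = 0.13, RR 1.20 (95% CI 0.95 to 1.53). There is no significant difference, but non-inferiority is not shown.
- 280 against 236: P = 0.04 (worse), RR 1.19 (95% CI 1.007 to 1.397). There is a significant difference, yet the upper limit is just inside the margin.

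**The case against.** A reader might infer that the margin is never tested and that the trial cannot answer its own question. The article does not support that. It states the margin, the one-sided error rate and its equivalence to a two-sided 95% interval, and it promises 95% intervals on the same outcome in both analysis sets. The raw material for a non-inferiority assessment is there. A full protocol or analysis plan, not shown, may hold the linking rule, and an article may leave that detail out.

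Chi-square also has a legitimate place. The abstract's aim includes superiority, and chi-square is an ordinary test for that.

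A reader might also infer that the 2.5% error rate is lost throughout. That does not follow either. The article never says that P above 0.05 will be taken as non-inferiority, so the percentages in Step 3 are conditional on that reading. Even then the excess is clear at 5% control risk, modest at 7.5% and absent at 10%, where 1.1% is below 2.5%.

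All of this limits the size of the point, but the mismatch remains. The article does more than leave a rule out. It names a primary test, a significance threshold and an effect scale, and none of the three is the one the design calls for. An analysis plan that tested the hypothesis would have to depart from this section.

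**Conclusion.** The point holds as a mismatch between the stated primary analysis and the stated design, and it should be corrected before the data are analysed. The named test addresses only the superiority half of the aim, and the named interval has no margin on its scale.

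The practical size depends on the control risk. Within the planned 5% to 10%, reading non-significance as non-inferiority at a true relative risk of 1.40 would err in 17% of trials at the low end and 1.1% at the high end, against 2.5% for the margin test. With no true difference, between 22% and 0.6% of trials would be non-significant and still fail the margin.

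These figures assume 2362 analysed per arm, independent infants, the log-scale interval for the relative risk and, for the error rates, a reading of non-significance that the article does not itself state.

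**What to change.** Replace the chi-square sentence in Data analysis with wording such as:

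> The primary estimate is the relative risk (home / hospital) of poor clinical outcome with a two-sided 95% CI. Non-inferiority is concluded if the upper limit is <1.40; superiority is then concluded if the upper limit is <1.00.

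Keep the risk difference with its interval as a supporting estimate. The per-protocol and intention-to-treat sets can stay as named.

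Restate Table 3 for this analysis: about 75%, 91% and 97% power at 5%, 7.5% and 10% control risk, in place of 88.4%, 97.5% and 96.6%. The sentence claiming more than 88% power across 5% to 10% must change with it.

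Cost: a paragraph of wording and a revised table, with no extra patients or data. The downside is that stated power becomes less favourable at 5% and 7.5% control risk. That reflects testing the margin on the scale on which it was set.

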### Quality control and assurance

All study teams (screening, enrolment, randomisation and outcome assessment teams) will have study supervisors who will support adherence to the manual of operations. The quality assurance team will conduct regular standardisation exercises, oversight and monitoring of all study activities through regular and random visits and checks of the proportion (10%) of all completed study forms. A site preparation review will be conducted before the initiation of the study. This will include the standardisation of practices and measurements. To ensure the quality of study implementation, external oversight and support will be provided by WHO staff and study consultants.

### Quality of care in hospitals

The hospital infant care services will be strengthened regarding human resources and capacity building through training, processes and standard operating procedures (SOPs), ensuring continuous availability of standard quality antibiotics and basic support for routine care. The “minimum” quality of care will be according to the WHO pocketbook for hospital care for children [4], which includes keeping the baby warm and providing kangaroo mother care to prevent hypothermia, encouraging a mother to breastfeed frequently to prevent hypoglycaemia, fluid management when required, basic laboratory support, and oxygen therapy when needed [4]. The hospital team will be oriented on the study protocol and recommended treatment protocols, including information on indications for changing the treatment regime. Regular visits to assess the quality of care at the hospitals will be made by an experienced paediatrician / neonatologist. Medical equipment provided to the participating hospitals for the study will remain there after the completion of the study.

### Training of health workers and study staff

The study staff who will perform screening, enrolment, and outcome measurement will be trained using a standardised study Manual of Operations. Data will be collected by research staff on standardised data collection forms. During training, emphasis will be placed on maintaining Good Clinical Practice (GCP) standards. All research staff will be trained in rapport-building and communication with mothers / caregivers. The screening and enrolment study staff will be trained to introduce the study to potential participants, administer the consent form, assess for clinical signs and eligibility, and correctly complete all relevant study forms. The outcome measurement staff will be trained in the definitions of outcomes and on their standardised assessment, as well as completion of the outcome assessment forms.

### Standardisation and refresher training

Periodic standardisation exercises every quarter will be carried out for study staff, supervisors and IOAs to the identification of clinical signs to maintain their clinical skills. The study sites will also develop a system of periodic refresher training for health workers, supervisors and IOAs through clinical practice and / or video demonstrations. In addition, periodic centralised standardisation exercises and refresher training will also be conducted by WHO for the study staff.

### Logistics and commodities

All sites will be equipped with necessary medicines, equipment and logistics for pneumonia case management, such as oral amoxicillin 250 mg (or 125 mg) dispersible tablets, pulse oximeter with accessories, digital and mercury thermometers, digital weighing scales, respiratory rate counting timers / digital timers and other necessary materials centrally through the WHO supply division to maintain standardisation. The study teams will monitor the equipment for periodic standardisation and replacement of faulty devices, if any. The consumables will be replenished as per need.

### Supervision

A study supervisor will supervise all study staff. A supervisor will periodically validate a proportion of young infants who are assessed as potential enrolment to ensure quality. Supervised accompanied visits and independent unaccompanied visits will be carried out regularly by the supervisors. Video calls or video clips of signs, e.g. severe chest indrawing, will also be used in real-time to allow supervisors to monitor the correct identification of signs from time to time. Principal investigators and co-investigators will also make random visits to check the performance and quality of the trial.

Periodic meetings of the research implementation teams will be held to review enrolment, performance, observations and follow-up problems and identify solutions / required actions to overcome those. Action points will be followed up on in the next meeting.

### Monitoring

All the sites will submit monthly progress reports to the coordinating site at the WHO, which will be reviewed, and feedback will be provided. Regular conference calls will be held with all sites to discuss the progress and critical issues of the study. Data-based monitoring, as well as verification of serious adverse event (SAE) forms, will be carried out by the DCC in collaboration with the WHO study coordination team. Investigators and study coordinators will randomly visit the field sites to observe study staff, supervisors and IOAs performing their activities. They will cross-check a small proportion of collected case report forms (CRFs) and share observations with supervisors and IOAs.

### External monitoring

The WHO study coordinating team will visit each site before the initiation of the study to assist in the preparation and planning of the site implementation of the protocol and study procedures. Due to restrictions on travel because of the COVID pandemic, virtual visits and the monthly online meeting will also be held. Country-based WHO monitors or other monitors will visit each site at least once or twice a year to monitor the progress and observe the procedures using a checklist to monitor clinical trials. It will include assessment and enrolment procedures, clinical practices such as counting respiratory rate, identifying danger signs, conducting pulse oximetry, and review other study procedures, and data management. Various logbooks will be checked. A proportion of completed electronic CRFs will be checked, and all SAE reporting forms will be reviewed. WHO monitors will also observe physician awareness and will meet with the regular hospital staff. In addition, they will make a home visit to those who are receiving treatment in the intervention arm and talk with the parents. When possible, the monitors will meet with the community groups’ members, ministry and district health officers, and programme managers at different levels. Recommendations arising from the site monitoring visits will be shared and discussed with the principal investigators and other project staff at the site office, and follow-up actions will be undertaken.

### Ethical considerations

The protocol has been approved by all the local institutional ethical review committees at the study sites and the WHO ethical review committee. Where required, national and regional / state approvals have been obtained. The safety of enrolled infants in this trial will be ensured by close monitoring and follow-up. The trial will follow CIOMS and GCP guidelines.

### Informed consent

Informed written consent will be obtained from parents / caregivers by a study nurse / physician at two stages, first at the time of screening / pre-enrolment and later at the time of enrolment, and will involve detailed verbal communication in the study participants’ native language to ensure comprehension of the trial and study procedures. If the parents/ caregivers are illiterate / unable to sign, then consent will be administered in the presence of a witness. All consent forms will be translated into local languages. Parents / caregivers of sick young infants will be provided basic information about the study and invited to consent for screening. Parents / caregivers of infants found to be eligible after the screening will be provided full information about the study and invited to have their infant participate in the study. The eligible infants will be enrolled if their parents provide informed consent and will be randomised to either one of the treatment arms according to the study approach. Illiterate parents / caregivers will be asked to give a thumbprint on the consent form; literate parents / caregivers will be requested to sign the consent form. Study staff will be trained in the study methodology, including obtaining consent.

### Patient safety

The study procedures and data collection will not pose any significant physical, psychological, social, legal or other kinds of risks to the participants. Clinical assessment and illness management, including the provision of drugs to be used in this study, are routinely used in clinical practice. Every enrolled subject will be followed up till the completion of treatment and assessed on day 15 of the enrolment. Poor clinical outcomes (except deaths) will receive an appropriate change of antibiotic therapy according to standard clinical practice. Those needing hospitalisation will be referred and admitted to the sub-district / district / tertiary care hospitals immediately for appropriate management as required. Other discomforts to caregivers might include a longer waiting time for data collection. However, the procedures will be explained in detail, and any queries by parents will be answered. The mobile phone number of the responsible study staff and study supervisors will be provided to all participants’ caregivers so that they could reach them if needed.

We will counsel and empower the mother / caregivers / families at enrolment, and all follow-up visits to 1) recognise danger signs or signs of illness and seek care and 2) know when to return to the hospital for follow-up care. We will train the mother / caregiver / family on the quantity, frequency and process of giving oral antibiotics at home. Systems will be in place in the hospital to provide emergency and rescue care in case of any adverse event or facilitate referral to a higher facility if required.

### Adverse events – documentation, reporting and response

Any adverse event that occurs after enrolment will be recorded on an adverse event reporting form by the treating nurse / physician. In case of an SAE, the study staff will contact the study supervisor and IOA. The IOA will document the SAE and convey the information to the study coordinator / investigator. An SAE, like death, anaphylactic reaction, severe diarrhoea, and a disseminated or severe rash will be reported to WHO within 48 hours of the occurrence. These cases will be (except, of course, the ones who unfortunately die) provided appropriate treatment and will be followed up. In case of other minor adverse effects, such as mild rash etc., the treatment will be continued. WHO will periodically report SAEs to the DSMB.

